**Figure 1 F1:**
[figure not shown]
**Cohort ascertainment, randomization and study timeline.** HI, hospital inpatient rehabilitation; HO, hybrid home program.

This trial is a two-arm parallel RCT (Figure 1). The two study groups are: (1) hospital inpatient (HI) and (2) home-based group (hybrid home program (HO)).

Potential participants who are unwilling to undergo randomization will be invited to participate in a third, non-randomized, observational group, who will be followed up 6 months after surgery. This third group will permit the detection of a possible preference effect amongst recruited participants. If study recruitment is biased towards people with a preference for inpatient rehabilitation, there is a risk that participants randomized to the inpatient arm will, in part, report superior outcomes compared to those randomized to the home program because they received their preferred program. If no such superiority is observed when we compare those who were randomly allocated to usual care and preferred inpatient rehabilitation to those who opted to receive usual care (those in the observational arm), then it is possible that any preference effect (if present) is not strong.

The study is expected to take up to 51 months, consisting of 30 to 33 months for recruitment and randomization, 12 months for follow-up of the final participants, and 6 months for analysis.

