#### Primary

The primary outcome is walking distance at 6 months post-surgery measured using the 6MWT [24-26]. A functional outcome based on a physical test is a novel choice as a primary outcome in this field given that the convention with most TKA rehabilitation studies is to focus on patient-reported outcomes [16,25-28]. The decision to employ measured mobility as the primary outcome was based on multiple factors. First, functional mobility is a composite of several factors targeted in rehabilitation programs after TKA such as lower limb strength, knee range of motion, and balance [25,26,28-30]. Second, a functional outcome is more likely to be directly influenced by the intervention (rehabilitation), and the intervention aims to improve walking. Third, the 6MWT is highly reproducible within the individual [31]. Fourth, it is likely to be less susceptible to misinterpretation and less culturally sensitive than patient-reported outcomes. Fifth, the test does not appear to suffer from the floor or ceiling effects associated with many patient-reported outcomes [21]. Sixth, an observer-measured outcome is less likely to be influenced by a preference effect compared to a patient-reported outcome, and this is particularly important when the intervention under examination cannot be blinded from the recipient. Together, these attributes mean the results for our primary outcome should be readily translatable to any TKA cohort.

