### Sample size

The primary end-point in this trial is functional mobility at 6 months post-surgery measured using the distance walked during a 6MWT. Seventy participants in each group (140 in total) will provide 80% power at a significance level of 5% to detect an increase in walking capacity from 400 m to 460 m between the HO and HI groups, respectively, in the 6MWT at 6 months post-surgery, assuming a SD of 120 m and a drop-out rate of <10%. The SD of 120 is a conservative estimate of the SD of the mean 6MWT at 6 months [18,25]. Using a 0.5SD criterion, this sample will be powered to detect a moderate effect size of 60 m difference in walking distance. If the actual SD of the sample collected is smaller than the assumed value, say 100 instead of 120, the study will remain powered to detect a moderate effect size of 0.5SD.

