#### Analyses subsets

Data analysis will be completed using the principle of intention-to-treat [36]. We will include all randomized participants regardless of level of compliance with the protocol. The primary outcome variable is distance measured using the outcome of a 6MWT at 26 weeks.

Analysis of covariance will be used for this primary outcome, with treatment group as the main study factor and walking distance at baseline, weight, BMI, co-morbidities and patient preference as covariates. For participants with a missing outcome measure at 26 weeks, an imputation method will be used [37,38].

The secondary outcome variables include the 6MWT at 10 and 52 weeks post-surgery, the 15 m walk test, EQ5D, Oxford Knee Score, KOOS and knee ROM at most post-surgery time points.

Mixed model analyses will be used for the continuous variables measured repeatedly at 10, 26 and 52 weeks to estimate the treatment group by time effects. These analyses incorporate the missing data that may occur at the follow-up occasions. Baseline measurements of the outcome variables, together with factors such as weight, BMI, co-morbidities and patient preference, will be included as covariates [39]. For the binary outcome measured at 10, 26 and 52 weeks (knee flexion ≥100 degrees or ≤100 degrees), a Generalized Estimating Equation model will be used to test the treatment effect, with the adjustment of the covariates as above.

For the analyses involving the observational arm, the change score in the primary outcome will be compared between the observational group and those in the randomized home group adjusting for other covariates. A lack of significant difference in scores between the two groups will suggest there is no strong preference effect in this trial and we may not need to include preference as a covariate in the RCT analyses. To be consistent with the two RCT groups, we will aim for a minimum 64 participants in the observational group.

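### A non-significant, non-randomised 6MWT comparison is read as suggesting no strong preference effect, and may decide whether preference stays in the randomised analysis

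*Protocol article*

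**What the plan says.** Three places in the protocol article bear on this.

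- **Text under Figure 1 (Recruitment and consent).** Patients who decline randomisation are invited into an observational group so that a preference effect can be looked for. The comparison described is of "those who were randomly allocated to usual care and preferred inpatient rehabilitation to those who opted to receive usual care". Only Home participants who wanted inpatient care enter it.
- **Analyses subsets.** Here "the change score in the primary outcome will be compared between the observational group and those in the randomized home group", with covariate adjustment and no restriction by stated preference. The decision rule follows: "A lack of significant difference in scores between the two groups will suggest there is no strong preference effect in this trial". In that case preference may not be needed as a covariate in the RCT analyses. The target of at least 64 observational participants is justified only by consistency with the randomised groups. No margin, interval criterion or power is given for this comparison.
- **Outcome measures, Primary.** The 6MWT was chosen partly because "an observer-measured outcome is less likely to be influenced by a preference effect compared to a patient-reported outcome".

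The Abstract says that preference stated before randomisation will be accounted for. The ANCOVA and mixed models in Analyses subsets list it as a covariate. Baseline and other data records it before surgery as home, inpatient or either.

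**The concern.** Failure to reject a null hypothesis is used as evidence that an effect is not strong, in a comparison that was neither randomised nor sized for the purpose. Three features add to the difficulty.

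- The two sections define different Home comparators, so it is unclear which effect the comparison estimates.
- The conclusion is drawn for the trial as a whole and governs the RCT analyses, which include KOOS, Oxford Knee Score and EQ-5D. It rests on an outcome that the protocol itself considers less prone to preference than patient-reported measures.
- A covariate set that the protocol otherwise fixes in advance becomes dependent on outcome data.

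At stake is a reassuring statement about preference that the data may not support, in an open-label trial whose patient-reported outcomes are the more exposed to it.

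**Working it through.** **Inputs.** From Sample size: 70 per arm, 80% power, 5% significance, a 60 m difference ("to detect an increase in walking capacity from 400 m to 460 m between the HO and HI groups"), SD 120 m and drop-out below 10%. That section also considers an SD of 100 m. From Analyses subsets: at least 64 in the observational group. Assumptions, because the documents give no figure: the share *f* of the Home group that preferred inpatient care, and the SD of the adjusted change score. If the SD is 120 m at both visits, the unadjusted change score has SD 120·√(2(1−ρ)), which is 120 m at ρ = 0.5 and 76 m at ρ = 0.8. A range of 80 to 120 m is therefore used.

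**The plan's own figure.** n per arm = 2·(1.960 + 0.842)²·(120/60)² = 62.8, so 63; 63/0.90 = 70. The stated sample size reproduces with a two-sided test. It concerns the Inpatient–Home contrast, not the preference contrast.

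**Precision of the preference contrast.** With 64 per group, SE = 120·√(2/64) = 21.2 m and the 95% half-width is 1.96 × 21.2 = 41.6 m. With 63 Home participants (70 less 10%) it is 1.96 × 120·√(1/64 + 1/63) = 41.7 m. A non-significant estimate can lie anywhere up to about 41.6 m, so its upper confidence limit can reach almost 83 m. Non-significance alone does not exclude 60 m.

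**Chance of missing an effect.** If each Home participant who preferred inpatient care loses *d* = 60 m and the others lose nothing, the Home arm as a whole is lower by *f·d*. Power ≈ Φ(*f·d*/SE − 1.96), and the chance of a miss is 1 − power:

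| SD (m) | Half-width (m) | *f* = 0.25 (15 m) | *f* = 0.5 (30 m) | *f* = 0.75 (45 m) | *f* = 1 (60 m) |
|---|---|---|---|---|---|
| 120 | 41.6 | 90% | 71% | 44% | 19% |
| 100 | 34.6 | 87% | 60% | 28% | 8% |
| 80 | 27.7 | 82% | 44% | 11% | 1% |

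At SD 120 m, a 60 m effect is detected more often than not only when *f* exceeds about 41.6/60 = 69%.

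**The narrower comparator.** With *f* = 0.5, the contrast described under Figure 1 is 32 against 64. SE = 120·√(1/32 + 1/64) = 26.0 m, and power for 60 m is 64%. This removes the averaging but is still not adequate power.

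**What the covariate can do.** Suppose there is no rehabilitation effect, half prefer inpatient care, and those among them allocated Home lose 60 m. The Inpatient–Home difference is 60 m in those who preferred inpatient care and 0 m in the rest, so the average is 0.5 × 60 + 0.5 × 0 = 30 m. Randomisation balances preference in expectation, so a main-effect term leaves this 30 m unchanged. Only the effect by preference stratum shows it.

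**Precision of that alternative.** With 126 analysed and a 50:50 split there are 31.5 per cell. The interaction SE = 120·√(4/31.5) = 42.8 m, a 95% half-width of about 84 m.

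**The case against.** The strongest reply has five parts.

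- **The whole Home group may be the right comparator.** The bias that preference puts into the Inpatient–Home contrast is the average over the arm, *f·d*, and the Analyses subsets comparison targets exactly that. This stands. A reader might infer that this section uses the wrong Home group; the documents do not show it. They show two different contrasts that need reconciling.
- **A miss is not the usual result under all conditions.** A reader might infer that a real effect would usually or nearly always go undetected. That depends on *f* and the SD, and the documents give neither for this comparison. The text under Figure 1 worries about recruitment tilted towards inpatient preference, which means a high *f*, and at *f* = 1 a 60 m effect is detected about 81% of the time. Self-selection can also create a difference, so the error does not run only towards reassurance. All this stands.
- **The wording is hedged.** The rule suggests that there is no strong effect and says preference may not be needed. True, but it still links non-significance to the model.
- **Preference and the 6MWT are not ranked as strongly as a reader might infer.** The text calls preference a conditional risk, not the main threat to validity. It calls an observer-measured outcome less prone to preference than a patient-reported one, not the least prone of all; gait speed and knee range of motion are observer-measured too.
- **The consequence is limited.** Dropping a main-effect covariate does not move the expected treatment estimate, and the interaction is less precise than the contrast criticised here. Both are correct. They argue for reporting estimates without a pass/fail rule; they do not defend the rule.

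**Conclusion.** The concern holds in a bounded form. The protocol draws a conclusion about preference from non-significance in a self-selected comparison with a 95% half-width of about 42 m at SD 120 m (about 28 m at SD 80 m). Such a result cannot rule out an effect as large as the trial's own 60 m target.

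Under the assumption that half the Home group preferred inpatient care, a 60 m effect in those participants is missed about 71% of the time at SD 120 m and 44% at SD 80 m. If all preferred it, the figure is about 19% at SD 120 m. These rates rest on an assumed share, an assumed SD and no confounding.

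Independently of those numbers, two sections define different Home comparators, the result is extended to patient-reported outcomes that it does not examine, and the rule conflicts with the covariate set in the Abstract and earlier in Analyses subsets. The randomised primary comparison is not invalidated. The interpretation of preference, and the stability of the pre-specified model, are what need correcting.

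**What to change.** 1. Delete the sentence in Analyses subsets that reads a non-significant difference as no strong preference effect, with the option to drop the covariate. Keep preference in the pre-specified covariate set whatever the observational comparison shows.
2. Reconcile the text under Figure 1 with Analyses subsets on which Home participants are compared, and state whether the target is the effect in those who preferred inpatient care or the average over the arm.
3. Report the observational contrast descriptively, as an estimate with 95% CI, and acknowledge self-selection.
4. Within the randomised arms, report the treatment effect by pre-surgery preference, with the interaction estimate and 95% CI, for 6MWT and at least one patient-reported outcome such as KOOS or Oxford Knee Score.

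The cost is analysis wording only, because preference is already collected before surgery. The drawback is imprecision: with an interaction SE of about 43 m at a 50:50 split, item 4 must be presented as an estimate, not as a test that preference passes or fails.

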### Hospital inpatient rehabilitation

Those allocated to HI will be admitted to the adjacent rehabilitation hospital for 10 days. As per the private sector, HI participants will receive twice-daily supervised physiotherapy comprising 1 to 1.5 hour class-based exercises and 1 to 1.5 hour one-to-one therapy. Prior to discharge, participants will be familiarized with the home program as described below.

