### Hybrid home program (standard care)

The HO will be based on what is standard care in the local health district, which is broadly based on the home program utilized in our most recent RCT [18]. The original home program was informed by guidelines for exercise in the elderly [20] and those with osteoarthritis [21]. Approximately 2 weeks post-surgery, participants allocated to the HO will attend one group-based outpatient exercise session in the physiotherapy department where the home program will be rehearsed and exercises individualized as required due to co-morbidities. The program comprises general aerobic components as well as general functional and muscle-specific exercises focused on restoring knee mobility, lower limb strength, and normal neuromuscular co-ordination and gait patterns.

Participants in both treatment arms will be encouraged to attend one to two classes from post-operative weeks 3 to 8 to encourage exercise progression and discuss any ongoing issues with the therapist. Participants will receive a booklet detailing the home program, and will be permitted to contact the therapist by phone in this period.

All participants will be required to complete a diary detailing program adherence, healthcare utilization, and social costs relating to carer-burden. Participant attendance at the outpatient classes will also be obtained from the treating physiotherapist.

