For the sensitivity analysis, the above analysis used for the primary and secondary outcome variables will be performed ‘as-treated’, analyzing patients according to the treatment they actually received and excluding those with missing outcome measures. It will only include patients who were compliant with the intervention protocol. Compliance for the HI group will be defined as attendance of a minimum of 7 days of inpatient rehabilitation, along with attendance at no less than two outpatient sessions. Compliance for the HO group will be defined as attendance at no less than two outpatient sessions. There will be procedures put in place to minimize loss to follow-up, such as obtaining multiple contact details at time of consent and reminders that assessments are due. The age, gender and height of participants will be used as stratification variables in the randomization procedure via a minimization algorithm. The mixed model analysis indicated above will include these three variables as additional covariates to incorporate the possible within-treatment group correlation associated with stratification [39].

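### The two-session compliance rule is the inpatient arm's planned maximum but the home arm's planned minimum, so the compliers-only sensitivity set is selected differently by arm

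*Protocol article*

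**What the plan says.** Three sections of the protocol article bear on this.

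- **Hospital inpatient rehabilitation.** The stay is 10 days. "Prior to discharge, participants will be familiarized with the home program as described below". The introduction to the home program therefore falls inside the inpatient stay.
- **Hybrid home program (standard care).** At roughly two weeks after surgery, "participants allocated to the HO will attend one group-based outpatient exercise session in the physiotherapy department". After that, "Participants in both treatment arms will be encouraged to attend one to two classes from post-operative weeks 3 to 8".
- **Analyses subsets.** The main analysis is by intention to treat and takes in everyone randomized. The sensitivity analysis repeats the primary and secondary analyses by treatment received and leaves out those without outcome data. It is then narrowed further: "It will only include patients who were compliant with the intervention protocol". Compliance in the inpatient arm (HI) has two parts. One is a minimum stay of 7 days. The other is stated as "along with attendance at no less than two outpatient sessions". For the home arm (HO), "Compliance for the HO group will be defined as attendance at no less than two outpatient sessions".

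**The concern.** A compliance rule should pass someone who did what the plan asked. Here one threshold is applied to two arms whose planned number of outpatient sessions differs by one. The HI participant has to attend everything on offer; the HO participant has to attend only the least that is planned. The two halves of the sensitivity set are then filtered by different degrees of class attendance, and randomization no longer protects the comparison.

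A second difficulty sits in the same paragraph. The analysis is described as as-treated, is limited to compliers (a per-protocol restriction), and is limited to complete cases. These are three separate departures from intention to treat, made together.

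At stake is the usefulness of the one sensitivity analysis that the article describes. Readers would turn to it to learn whether the main result holds among people who received the programs as planned.

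**Working it through.** **1. The plan's own figure.** Inputs from Sample size: difference 60 m, SD 120 m, 80% power, 5% significance (two-sided assumed), drop-out below 10%. n per arm = 2 × (1.960 + 0.842)² × (120/60)² = 62.8, so 63; 63/0.90 = 70. The stated 70 per arm is reproduced. It does not depend on the compliance rule. The 63 is used below as the evaluable number per arm.

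**2. Planned outpatient sessions.**

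| | Week-2 session | Classes, weeks 3 to 8 | Planned total | Threshold |
|---|---|---|---|---|
| HI | 0 (covered before discharge) | 1 to 2 | 1 to 2 | 2 |
| HO | 1 | 1 to 2 | 2 to 3 | 2 |

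**3. Who is kept.** Take HI participants with at least 7 inpatient days and HO participants who attended the week-2 session.

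| Classes attended | HI total | HI kept? | HO total | HO kept? |
|---|---|---|---|---|
| 0 | 0 | no | 1 | no |
| 1 | 1 | **no** | 2 | **yes** |
| 2 | 2 | yes | 3 | yes |

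The arms part company only in the middle row, and one class is within what the protocol invites.

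**4. How many are dropped.** The article gives no attendance figures, so these are illustrations.

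- *Everyone attends one or two classes, all HO attend week 2, all HI stay at least 7 days.* If a fraction f attends only one class, HI kept = 63 × (1 − f) and HO kept = 63. With f = 25%, 50%, 75%, HI kept is about 47, 32, 16. The standard error is 120 × √(1/n_HI + 1/n_HO), which is 23.1, 26.2 and 33.8 m. Power to detect 60 m falls from 80% to about 74%, 63% and 43%. Under the same assumptions, a rule of at least one class in both arms keeps 63 and 63.
- *Each session attended independently with probability a, two open to HI and three to HO.* HI passes with a²; HO passes with 3a² − 2a³. For a = 0.7, 0.8, 0.9 that is 49%, 64%, 81% against 78%, 90%, 97%: gaps of about 29, 26 and 16 points.
- *As above, but every HO participant attends week 2.* HO passes with 1 − (1 − a)², that is 91%, 96%, 99%. The gap is 2a(1 − a): 42, 32 and 18 points.

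**5. How large a shift selection alone could cause.** Assume no true effect, a normal model, all HO kept, and correlation ρ between propensity to attend and walking distance. If a share q of HI is kept, the shift is ρ × 120 × φ(c)/q, where c is the normal cut-off that leaves q above it.

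- q = 0.50: φ(c)/q = 0.798, so |ρ| = 0.1 to 0.3 gives about 10 to 29 m.
- q = 0.75: φ(c)/q = 0.424, so |ρ| = 0.1 to 0.3 gives about 5 to 15 m.

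The sign of the shift is the sign of ρ, which the article does not supply. The size is before covariate adjustment.

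**6. The mixed label.** Take someone allocated to HI who goes straight home. By treatment received they belong with HO; by HI's compliance rule they are out. The text does not say which governs. Missing 26-week outcomes are imputed in the primary analysis and excluded here, so the handling of missing data changes at the same time.

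**The case against.** The best defence is that HI may get the week-2 session too. The abstract says the inpatient stay is followed by usual care, meaning the hybrid home program, and the week-2 session is part of that program. Were that so, both arms would have two to three sessions and the asymmetry would vanish. The arm protocols are in a Standard Procedures Manual that is not shown. This reading is open but weaker. The Hybrid home program section ties the session to those allocated to HO and only afterwards turns to both arms, and HI participants are introduced to the program before discharge. Clearance by about day 5 plus 10 inpatient days also puts discharge near day 15, about when the session is held. It is also true that encouraging one to two classes sets no upper limit. Either way, the sections need reconciling.

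A reader might infer that the rule keeps the most motivated inpatients and so flatters inpatient rehabilitation. The documents do not support that direction. The classes also exist so that participants can raise continuing problems with the therapist, so a second class may draw people who are recovering slowly, which would push the contrast the other way. Nor are the gaps in step 4 a measure of bias: they are differences in inclusion under assumed attendance. The planned covariates (baseline distance, weight, BMI, co-morbidities, preference) would absorb part of any selection.

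Finally, it is fair to say that the primary inference is untouched, and that a request for a further missing-data analysis would concern detail commonly left to an analysis plan. No such request is made here.

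**Conclusion.** The point holds in a limited form. On the better-supported reading, the compliance rule does not fit the intervention sections: HI must reach its planned maximum and HO only its planned minimum. HI participants who complete the stay and attend one class are removed, while HO participants with the same later attendance stay. The set is therefore selected differently by arm, with bias of unknown direction. Its size cannot be determined from the article; steps 4 and 5 show only that moderate single-class attendance would be enough to unbalance the arms noticeably. The threshold can be met in HI, so the arm is not emptied.

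Separately, because treatment received, compliance and complete data are all imposed at once, a result that differs from intention to treat could not be traced to crossover, adherence or missing data.

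Both faults are confined to the sensitivity analysis. The intention-to-treat primary analysis and the sample size stand. The correction should be made, but it does not threaten the trial's main conclusion.

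**What to change.** 1. Reconcile the two intervention sections with Analyses subsets, stating whether HI participants are meant to have the week-2 session and which contacts count as outpatient sessions.
2. Define compliance for analysis relative to each arm's planned sessions. One form is at least one class in weeks 3 to 8 in both arms, plus the arm-specific component: the existing minimum of 7 inpatient days for HI and the week-2 session for HO.
3. Call this a per-protocol analysis by randomized arm. If an as-treated analysis is kept, do not also restrict it to compliers.
4. Report the result as supportive only. Some arm-specific selection remains, as in any per-protocol set where the arms receive different treatments.

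The cost is a few sentences and little extra analysis. Class attendance is already obtained from the treating physiotherapist. Recruitment was still active when the article was submitted and the analysts are to stay blind to allocation until the evaluation is complete, so the rule could be settled before allocation is revealed to them.
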